## Methods

### Design

This study is a closed cohort stepped wedge design in which the timing of the intervention is randomized by cluster, with the sequential crossover of clusters from control to intervention until all clusters have received the intervention. With this design, each cluster contributes data when they are participating in the intervention and when they are not. Stepped wedge designs are useful for several reasons. First, they allow all participants to receive the intervention, and each intervention arm can serve as its control, which decreases the number of units needed. Second, the design is practical in a situation with limited resources where the intervention logistically cannot be carried out all at once. Third, the design allows researchers to examine any effects of time on the intervention’s effectiveness [36,37]. Baseline data on current dietary intake, food security, malnutrition, technology use and attitudes, physical activity, social isolation, loneliness, and demographics were collected from all participants at Time 0. Each of the 12 centers was randomly assigned to one of 2 cohorts. Participants in Cohort 1 received the intervention first. Once Cohort 1 participants finished the intervention, a crossover occurred as Cohort 2 participants began the intervention. At the 12-month time point, the second cohort completed the intervention. Data will be collected for both groups each time point from T0 to T3 (Figure 1).

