#### Randomization and Allocation

Twelve out of the 14 centers participated in the study and were stratified by congregate meal participant enrollment and attendance as large (>100 participants), medium (50‐100 participants), and small (<100 participants) and randomly assigned to one of 2 start times: immediately (Cohort 1) or 6 months later (Cohort 2). Site randomization by a statistician occurred after participant recruitment; however, the treatment condition was not revealed to the participants. Neither the study participants nor the study staff were blinded to the treatment conditions.

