#### Participant Retention and Remuneration

Participants received compensation of a US $20 local grocery store gift card for each data collection event (T0, T1, T2, and T3). Additional rewards were built into the intervention to encourage participation and retention. Cohort 2 participants served as the active control group when not receiving the intervention. The active control consisted of monthly presentations on wellness topics not related to nutrition and bingo games led by our research team, in which they could win a US $5 local grocery store gift card. Furthermore, voluntary peer navigators, who were participants enrolled in the study and attending the center, were recruited from most sites to assist any participant requiring extra help with Zoom (Zoom Video Communications, Inc) session login, survey completion, or troubleshooting challenges within their capacity.

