### Measurements

Table 2 lists all the measurements incorporated in the study.

**Table 2. T2:** Overview of measurements applied in the digital nutrition intervention study.

Measurement		Data collection timeline	Outcomes
Diet Quality Score		Measured at all data collection timepoints.	Developed to assess diet quality and nutrition risk [38]. Completed within 15 minutes and used to assess the Diet Quality Score [49]. Score based on overall diet quality (greater than 75=not at risk, between 60‐75=possible risk, less than 60=at risk) [50].
Healthy Eating Index (ASA24 Food Recall)		Prior, during, and after the assigned cohort intervention.	Measurement of dietary quality on recommendations from the Dietary Guidelines for Americans [51]. Completed using the Automated Self-administered 24-Hour Dietary Assessment (ASA24) online tool developed by the National Cancer Institute [52]. Research team will assist participants in the completion of the ASA24 food recall. Scoring is on a scale of 1 to 100 for the following food groups: fruits, vegetables, greens, whole grains, dairy, protein, seafood, plant proteins, fatty acids, refined grains, sodium, added sugars, and saturated fats [51].
Food security		Measured at all data collection timepoints.	Helps to determine financial barriers for safe access to food in the last 3 months [53]. The 10-question US Adults Food Security Survey Module will be used to assess food security in the following categories and score: 0=high food security, 1‐2=marginal food security, 3‐5=low food security, ≥6=very low food security [54].
Physical Activity Scale for the Elderly (PASE**)**		Measured at all data collection timepoints.	Used to assess self-reported physical activity in community-dwelling older adults over 7 days by adults aged 65 years and above [55]. PASE scores range from 0‐400 or more and are closely associated with grip strength and balance [55].
Short Physical Performance Battery (SPPB)		Prior, during, and after the assigned cohort intervention.	Developed by the National Institute of Aging to assess lower extremity functioning in older adults. SPPB includes gait speed, chair stand, and balance tests [56]. Overall scores can range from 0 (worst performance) to 12 (best performance) and are predictive of risk for frailty, mortality, nursing home admission, and disability [57].

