#### Statistical Models

##### Aim 1

Primary outcome data will be analyzed in Aim 1. For each of the 3 outcomes in Aim 1 (Dietary Quality Score and Food Security), at 3-month and 6-month periods, a 2-level multilevel model (MLM) will be constructed that examines change over time for individual participants within centers. MLMs consider that participants within a cluster (eg, a center) share characteristics that make them more like each other than participants at other centers. MLM has several distinct advantages over other modeling strategies: (1) MLM has greater statistical power given that the estimated standard errors are corrected for model dependency; (2) there is no need to assume or test for the homoscedasticity or sphericity assumptions, as these variance and covariance components are estimated within the MLM model. Depending on model complexity and whether the statistical assumptions are met, the models will be estimated via Bayesian estimation or maximum likelihood estimation with robust standard errors. For Level 1 (participant level), the outcome variable of interest will be modeled using pretest score on the outcome measure, treatment status (ie, control or experimental), and any nonequivalent baseline participant characteristics as covariates. Level 2 (center level) will model the cluster effect of centers on outcomes.

##### Aim 2

Data collected for Aim 2 represent our secondary research questions (eg, physical activity, technology knowledge and attitudes, social isolation, and loneliness). Data collected at all time points (Physical Activity Scale for the Elderly [PASE], technology knowledge and attitudes, social isolation, and loneliness) will be analyzed using MLM described in Aim 1. To minimize participant fatigue, data for this secondary research aim will be collected at defined intervals (T0, T1, and T2). These data will include the Healthy Eating Index and Short Physical Performance Battery (SPPB) to assess physical function. Differences between groups will be assessed at T2 for each outcome via 2-level covariate MLM models. Level 1 (participant level) will test whether treatment status (ie, control or experimental), pretest score on dietary quality, and food security, and any nonequivalent baseline participant characteristics predict outcomes. At Level 2 (center level), we will model the influence of the 7 centers.

##### Aim 3

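### For HEI and SPPB, Table 2's course-relative timing conflicts with Aim 2's T0, T1 and T2 readings and its control-versus-experimental test at T2

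*Protocol article*

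**What the plan says.** All references are to the protocol article.

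- **Measurements, Table 2.** The HEI and SPPB rows give the timing as "Prior, during, and after the assigned cohort intervention". Most other outcomes are taken at every time point. A further group has fixed early visits (baseline, 6 months) plus one 6 months after the intervention.
- **Statistical Models, Aim 2.** To limit fatigue, "data for this secondary research aim will be collected at defined intervals (T0, T1, and T2"), and HEI and SPPB are named as these data. The paragraph sets them apart from outcomes collected at all time points. The analysis follows: "Differences between groups will be assessed at T2 for each outcome via 2-level covariate MLM models". The Level 1 predictor is treatment status, control or experimental.
- **Randomization and Allocation.** Centers were "randomly assigned to one of 2 start times: immediately (Cohort 1) or 6 months later (Cohort 2").
- **Design.** "Data will be collected for both groups each time point from T0 to T3", and "At the 12-month time point, the second cohort completed the intervention".
- **Participant Retention and Remuneration.** Participants received a "gift card for each data collection event (T0, T1, T2, and T3"), so there are four T labels. The Abstract lists six visits: baseline and months 3, 6, 9, 12 and 18.
- **Statistical Models, Aim 1.** For the primary outcomes, "at 3-month and 6-month periods, a 2-level multilevel model (MLM) will be constructed".

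The visible text does not give T0 to T3 in months. Figure 1, which may, is not shown.

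**The concern.** A between-group test of treatment status needs one cohort still untreated when it is made. In this design that is possible only before Cohort 2 starts. A schedule tied to each cohort's own course puts Cohort 2's during and after readings past that point. Three readings labelled T0, T1 and T2 cannot both follow Cohort 2 through its course and leave it as the control at the third.

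What is at stake is the meaning of the HEI and SPPB result. If the measures are collected by Table 2 and T2 is taken as the after visit, the planned test has no control group. If the analyst then codes treatment status by randomized cohort, a program that works equally well in both cohorts would appear to have no effect on recalled diet quality or physical function.

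**Working it through.** **Inputs.** Course length is 20 weeks (Abstract): 140 days, or 4.6 months. Planned starts are month 0 for Cohort 1 and month 6 for Cohort 2. Planned courses therefore run over months 0 to 4.6 and 6 to 10.6. The month 6 visit is taken as before Cohort 2's first class. There is no stated figure to reproduce, because this is a check of consistency.

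**Step 1: common schedules.** Fix T0 at month 0 and choose T1 < T2 from months 3, 6, 9, 12 and 18. That gives 10 schedules. P = prior, D = during, A = after the cohort's own course.

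| T0, T1, T2 (months) | Cohort 1 | Cohort 2 | P, D and A in both? | Cohort 2 untreated at T2? |
|---|---|---|---|---|
| 0, 3, 6 | P D A | P P P | no | yes |
| 0, 3, 9 | P D A | P P D | no | no |
| 0, 3, 12 | P D A | P P A | no | no |
| 0, 3, 18 | P D A | P P A | no | no |
| 0, 6, 9 | P A A | P P D | no | no |
| 0, 6, 12 | P A A | P P A | no | no |
| 0, 6, 18 | P A A | P P A | no | no |
| 0, 9, 12 | P A A | P D A | no | no |
| 0, 9, 18 | P A A | P D A | no | no |
| 0, 12, 18 | P A A | P A A | no | no |

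Cohort 1 has all three kinds of reading in 4 schedules, Cohort 2 in 2, and both in none. Cohort 2 is untreated at T2 in one schedule (0, 3, 6), where all its readings are prior.

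**Step 2: own-course clock.** With visits at 0, 3 and 6 months from each start, Cohort 1 is read at study months 0, 3 and 6 and Cohort 2 at 6, 9 and 12. Table 2 is met for both, but both are treated at their T2.

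**Step 3: what the T2 contrast estimates.** Let d1 and d2 be the cohorts' effects, with no calendar change. For illustration, set both to 0.30 SD, the detectable effect in the power section.

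- Common month 6: d1 − 0 = 0.30 SD.
- Own-course after visit, coded by cohort: d1 − d2 = 0.30 − 0.30 = 0.00 SD.
- Month 12, coded by cohort: also 0.00 SD if the effect persists, with Cohort 1 read 12 − 4.6 = 7.4 months and Cohort 2 read 12 − 10.6 = 1.4 months after course end.
- Either all-treated case, coded by actual exposure: the predictor is constant and its effect cannot be estimated.

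**Step 4: the window for a concurrent control reading.** The Abstract reports completion in August 2023 (Cohort 1) and April 2024 (Cohort 2). Assuming an unbroken 20 weeks, Cohort 2 began between 1 April 2024 − 140 days = 13 November 2023 and 30 April 2024 − 140 days = 12 December 2023.

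- Shortest gap: 31 August to 13 November 2023 = 74 days = 2.4 months.
- Longest gap: 1 August to 12 December 2023 = 133 days = 4.4 months.

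These rest on program completion months, not assessment dates.

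**The case against.** **The Aim 2 test may be sound as written.** Common time points for both groups (Design) and the 3- and 6-month periods in Aim 1 both suggest that T2 is month 6 for everyone. The test then has an untreated Cohort 2, and the only defect is the timing phrase in two rows of Table 2. This stands. The other readings remain open, however. With four labels, six visits and T3 used for long-term impact, T0 to T3 could equally be months 0, 6, 12 and 18, which puts T2 after both courses. Figure 1 may show which instruction is wrong, but it cannot make both right if there are only three readings.

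**A reader might infer that no schedule at all could satisfy both statements.** The documents do not support that. Aim 2 does not use the word only. Readings at months 0, 3 and 6 for everyone, plus 9 and 12 for Cohort 2, would serve both the T2 test and Table 2. The limit to three readings is an inference from the omission of T3, the fatigue rationale and the contrast with outcomes taken at all time points. It is the natural reading but not a stated rule.

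**A reader might also infer that a false null is to be expected.** That needs T2 to be an all-treated visit and treatment status to be coded by randomized cohort. An analyst coding true exposure would find the variable constant and notice.

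**Table 2's wording may be loose.** For activities of daily living, the timing column gives a visit 6 months after the intervention, while the description gives 12 months. That weakens Table 2 as a literal schedule. Still, the HEI and SPPB rows tie timing explicitly to the assigned cohort, which no other row does.

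**Conclusion.** The conflict is real and does not depend on Figure 1, given that T0, T1 and T2 are the only HEI and SPPB readings. Cohort 2 is then either the control at T2, with no during or after reading, or treated at T2, with no control left.

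The size is conditional on what T2 means. With equal effects of 0.30 SD and no calendar change, the expected contrast is 0.30 SD at a common month 6. At an all-treated T2 coded by cohort it is 0.00 SD (at month 12, provided the effect persists). The 0.30 comes from a power section built on fruit and vegetable intake, so it illustrates the loss and does not predict an HEI or SPPB effect. The count of 0 in 10 schedules shows incompatibility, not likelihood.

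If T2 is month 6 for both cohorts, Aim 2 stands and Table 2 needs correcting. The point covers two secondary measures and says nothing against the Aim 1 contrasts.

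**What to change.** - State in Aim 2 that the HEI and SPPB between-group test is made at study month 6, before Cohort 2's first technology class, by randomized cohort.
- Correct the two Table 2 rows to months 0, 3 and 6 for both cohorts. Month 3 must stay: it is then the T1 reading that Aim 2 calls for, and it is Cohort 1's during reading.
- List any Cohort 2 readings at months 9 and 12 separately, as within-cohort data not used in the month 6 contrast.
- If Cohort 2 has no HEI or SPPB reading taken after Cohort 1 finished and before its own course began, drop the control-versus-experimental claim for these two measures and report within-cohort change as uncontrolled.

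**Cost.** If such a reading exists, the change is to wording and model specification, with no new data for the month 6 contrast. The reported dates suggest a window of about 2.4 to 4.4 months in which it could have been taken. That window has closed, so a missing reading cannot be recovered, and the cost is then the between-group claim for the two measures.

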## Results

The project was funded in October 2022. As indicated in the study progress (Figure 3), recruitment and screening started in June 2022. The research team recruited and screened 150 participants by the end of August 2022 at the 7 original target centers. Due to the low recruitment numbers, the number of centers and recruitment time were extended. Seven additional centers for recruitment were incorporated starting in September 2022. Power analysis was completed to ensure adequate recruitment numbers were met with the 14 centers. NIH was notified in writing of these changes. Fourteen centers were condensed to 12 centers (1 closed because of structural damage and 1 smaller center merged with a larger sister center).

A total of 578 older adults completed the screening, of whom 507 participants were eligible to participate in the study (88%). The 12 centers were randomly assigned into 2 study cohorts, which consisted of a total of 398 older adult participants. Cohort 1 consisted of 226 eligible participants, of whom 164 participants graduated from the program. Cohort 2 had 172 eligible participants, of whom 111 participants graduated from the program (Figure 4). Monthly bingo and informative presentations (nonnutrition and nonphysical activity–related) were conducted with Cohort 2 centers for engagement and retention. Focus groups were conducted for Cohort 1 postintervention in October 2023 and for Cohort 2 in June 2024 to assess the fidelity of the intervention. Data collection for Cohort 2 is currently ongoing. Preliminary data analysis is being conducted for all cohorts to evaluate the intervention’s outcomes.

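### The Aim 2 model at T2 omits baseline SPPB when SPPB is the outcome, leaves the HEI baseline ambiguous, and carries a leftover count of 7 centers

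*Protocol article*

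**What the plan says.** All of the modelling text is in the protocol article under Statistical Models.

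- **Aim 1.** The participant-level part of the model includes "pretest score on the outcome measure", with treatment status and any unbalanced baseline characteristics.
- **Aim 2, outcomes measured at every visit** (PASE, technology, isolation, loneliness). These "will be analyzed using MLM described in Aim 1", so each is adjusted for its own baseline.
- **Aim 2, outcomes measured at T0, T1 and T2 only.** "These data will include the Healthy Eating Index and Short Physical Performance Battery (SPPB) to assess physical function". They get a separate two-level model at T2. Its participant level tests whether "treatment status (ie, control or experimental), pretest score on dietary quality, and food security, and any nonequivalent baseline participant characteristics predict outcomes".
- **Center level of that model.** "we will model the influence of the 7 centers". The Results section states: "The 12 centers were randomly assigned into 2 study cohorts". The Abstract, Design, and Randomization and Allocation sections also give 12.

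Two other places bear on the point. The Baseline Equivalency section looks for imbalance in demographics, dietary intake and food security, and adds variables whose effect size lies between .05 and .25. Table 2 times HEI and SPPB relative to each cohort's own intervention (before, during and after it), not by T0, T1 and T2.

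**The concern.** The article itself fixes the covariates of this model, so this is not detail left to an unseen analysis plan. Diet quality and food security are the Aim 1 outcomes, and the wording looks carried over from there. For SPPB, a physical performance measure, they are likely to be weak predictors, while baseline SPPB is due at T0 under the same paragraph and is not used. No reason is given for treating SPPB differently from PASE or loneliness.

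At stake is the width of the interval for a secondary outcome compared at one visit across 12 centers, and whether a chance difference in physical function between the cohorts at T0 is adjusted for. The imbalance screen does not ensure this. It does not name SPPB, and even if SPPB were screened, a gap above .25 falls outside the stated range for adjustment.

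**Working it through.** **The plan's own figure.** None is given for the Aim 2 model. The nearest is in Power Calculations: 410 participants reduce to an effective 374, a design effect of 410/374 = 1.096. This reproduces as 1 + (7 − 1) × 0.016. I use the average number of participants per center instead, which gives a smaller gain for participant-level adjustment.

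**Inputs.**
- From the document: N = 398 participants in 12 centers (Results), so m = 398/12 = 33.2; ICC = 0.016 (Power Calculations).
- Assumed: correlation r between baseline and T2 SPPB of 0.5 to 0.7; a joint correlation of 0.2 between the listed covariates and SPPB; all 398 observed at T2; equal arms; two-sided alpha 0.05.

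**Variance without covariates**, in units of the simple two-group variance 4/N:
- between centers: 33.2 × 0.016 = 0.531
- within centers: 1 − 0.016 = 0.984
- total V = 1.515

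**Case A: adjustment reduces participant-level variance only**, V = 0.531 + 0.984 × (1 − r²).
- r = 0.2 (listed covariates): 0.531 + 0.945 = 1.475
- r = 0.5: 0.531 + 0.738 = 1.269
- r = 0.7: 0.531 + 0.502 = 1.033
- Gain against no covariate: 1.515/1.269 = 1.19 and 1.515/1.033 = 1.47
- Gain against the listed covariates: 1.475/1.269 = 1.16 and 1.475/1.033 = 1.43

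**Case B: between-center variance shrinks by the same fraction**, V = 1.515 × (1 − r²).
- Gain against no covariate: 1/0.75 = 1.33 and 1/0.51 = 1.96
- Gain against the listed covariates: 0.96/0.75 = 1.28 and 0.96/0.51 = 1.88

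**In terms of detectable effect**, MDE = (1.960 + 0.842) × √(4V/398):

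| Adjustment | MDE, case A | Power at 0.30, case A | MDE, case B | Power at 0.30, case B |
|---|---|---|---|---|
| listed covariates, r = 0.2 | 0.34 | 69% | 0.34 | 70% |
| own baseline, r = 0.5 | 0.32 | 76% | 0.30 | 80% |
| own baseline, r = 0.7 | 0.29 | 84% | 0.25 | 93% |

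Power is Φ(0.30/√(4V/398) − 1.960). These are normal approximations, so with 12 centers the power levels are somewhat optimistic. The contrast between rows is what matters.

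**Chance imbalance.** With arms of 226 and 172 (Results), the standard error of a baseline difference is √(1.515 × (1/226 + 1/172)) = 0.12 SD. A gap of 0.2 SD or more in either direction then has about a 1 in 10 chance (0.2/0.1245 = 1.61, two-sided p = 0.11). At r = 0.6, such a gap shifts the unadjusted estimate by 0.6 × 0.2 = 0.12 SD in that realisation.

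**Center count.** Results explains the 7: it was the original recruitment target. Seven centers were then added, and the 14 were condensed to 12 before randomization.

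**The case against.** Four objections have force.

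1. **HEI.** A reader might infer that HEI also loses its own baseline. The document does not establish that. Table 2 describes HEI as a measure of dietary quality, so the listed pretest may be HEI's own. If it is the screening-tool score instead, that is a proxy for the same construct. Only the ambiguity stands.
2. **Seven centers.** A reader might infer that five randomized centers would be left out of the analysis. Nothing says so, and the Aim 1 model clusters by center without giving a number. If all 12 are analysed, the 7 has no numerical effect.
3. **Bias.** A reader might call the 0.12 SD a bias. It is a shift conditional on a chance imbalance, and averaged over randomizations it is part of the sampling variance already counted in the precision argument.
4. **The imbalance rule.** It is loosely worded and ends by referring to any variables. If SPPB is screened, a 0.2 SD gap would bring it in. This is fair, but entry would then depend on an unclear screen instead of being fixed in advance as it is in Aim 1.

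It is also true that the size of the gain rests on assumed correlations. At r = 0.3 or below it is small: 1/(1 − 0.09) = 1.10 even in case B. The omission for SPPB stands after all of this.

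**Conclusion.** The point holds for SPPB: its T2 model as written leaves out the outcome's own baseline, unlike the model used for the Aim 1 outcomes and the other Aim 2 outcomes. For HEI the wording needs clarifying and no loss is shown. The count of 7 is a leftover that contradicts the 12 centers randomized.

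For SPPB the adjustment is worth about 1.2 to 1.5 times the sample if it acts on participant-level variance only, and up to 1.3 to 2 times if between-center variance shrinks equally. Both ranges assume r of 0.5 to 0.7, ICC 0.016 and about 33 per center. The cost is precision and unadjusted chance imbalance in a secondary outcome; the randomized comparison remains valid. The correction is worth making, but the point does not threaten the trial's primary conclusions.

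**What to change.** - In the Aim 2 model, add the T0 value of the outcome being analysed as a participant-level covariate: SPPB for SPPB, HEI for HEI. The listed diet quality and food security terms can stay if wanted. State which instrument the diet quality pretest refers to.
- Change the center count in Aim 2 from 7 to the 12 randomized centers.
- Reconcile the T0, T1 and T2 schedule in Aim 2 with Table 2. Cohort 2 starts 6 months after Cohort 1, so under Table 2 its pre-intervention measure need not fall at T0. Both cohorts need a T0 value for the adjustment to work.

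The first two changes take a sentence each. If HEI and SPPB were taken at T0 in both cohorts, as Aim 2 states, no new data are needed. If they were not, the article should say which baseline Cohort 2 has, and the adjustment cannot be applied as described.

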To assess the long-term impacts of the program at T3, Level 1 (time) will model the change in the outcome variables throughout the study (T0, T1, T2, and T3) within each participant. Specifically, each participant’s random intercept (eg, initial status) and the random slope over the 3 time periods will be calculated, and the time variable will represent the change in a particular outcome variable (ie, food security) over time within each participant. Level 2 (time nested within participant characteristics) will test whether treatment status (ie, control or experimental) and any nonequivalent baseline participant characteristics predict outcomes. If the ICC coefficient is greater than 0.10, a third level will be added to the model to control for clustering by center. Finally, participants will be clustered within centers (Level 3).

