Although the proposed intervention offers technology training, support, and access to the internet and devices, some limitations exist. A few participants may continue to experience challenges in understanding and using technology to engage in the online nutrition sessions conducted via Zoom. Moreover, the technical support and internet access provided by OATS ceased after the one-year service period, thereby restricting participants from using their devices except at the CMP site or locations offering complimentary Wi-Fi connectivity. Furthermore, the accuracy of survey completion may be affected by recall bias and introspective ability. To enhance the long-term sustainability of the project, mitigate associated costs, and strengthen the scope of incorporation into OAA services, it is important to investigate alternative options that offer low-cost internet access and affordable devices.

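### Aim 3 enters treatment as a participant-level label although both cohorts have been treated by month 12, so its coefficient does not estimate the long-term effect

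*Protocol article*

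**What the plan says.** The Aim 3 paragraph under Statistical Models sets out the model level by level.

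- **Visit level:** "Level 1 (time) will model the change in the outcome variables throughout the study (T0, T1, T2, and T3) within each participant". Time is the only term named here.
- **Participant effects:** "each participant’s random intercept (eg, initial status) and the random slope over the 3 time periods will be calculated".
- **Treatment:** "Level 2 (time nested within participant characteristics) will test whether treatment status (ie, control or experimental) and any nonequivalent baseline participant characteristics predict outcomes".

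The Design section describes a stepped wedge "with the sequential crossover of clusters from control to intervention until all clusters have received the intervention". On timing it says: "Once Cohort 1 participants finished the intervention, a crossover occurred as Cohort 2 participants began the intervention". It then adds: "At the 12-month time point, the second cohort completed the intervention". Randomization and Allocation gives the two start times as immediate and 6 months later. The abstract lists visits at baseline and at 3, 6, 9, 12 and 18 months. The text shown does not say which of these months are T1, T2 and T3.

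**The concern.** With visits at Level 1 and participants at Level 2, a Level 2 covariate takes one value per participant. In a stepped wedge, exposure changes within each participant, so it belongs at Level 1. A constant control/experimental label can only mean cohort, that is, early versus late start. By month 12 nobody is a control, and Aim 3 does not say what the label means after crossover.

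Long-term impact is one of three stated aims and covers both primary outcomes. If the benefit lasts in both cohorts, their means converge once Cohort 2 has been treated. The label coefficient then shrinks because the control cohort has been treated, not because the effect has worn off. A reader could take that shrinkage as a small or fading effect.

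The later visits also differ between cohorts in time since the intervention. Strengths and Limitations notes that "the technical support and internet access provided by OATS ceased after the one-year service period". If that year ran from each cohort's own start (an assumption), service ended at different calendar visits in the two cohorts. A cohort label cannot separate that from fading.

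**Working it through.** **The plan's own figures.** The article gives no figure for the Aim 3 model. Its power section concerns a simple group contrast. The stated 97.7% reproduces from effect size 0.41 and effective N 374: 0.41 × √(374/4) = 3.964; 3.964 − 1.960 = 2.004; Φ(2.004) = 0.977. It does not bear on this point.

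**Inputs from the article.** Starts at month 0 (Cohort 1) and month 6 (Cohort 2); Cohort 2 complete at month 12; visits at 0, 3, 6, 9, 12 and 18 months; cohort sizes 226 and 172.

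**Assumptions.** An effect D is reached by the end of the intervention and fully kept in both cohorts. A share x of D is present 3 months after the start (0, 0.5 or 1). There is no secular trend. Higher is better. Time is linear (one slope). For the mixed model, intercept and residual variance are 0.5 each, and slope variance is 0 to 0.01 per month².

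**Worked case, T0 to T3 = 0/6/12/18 months, in units of D.**

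- Expected means: Cohort 1 (0, 1, 1, 1); Cohort 2 (0, 0, 1, 1).
- Label main effect without slope variance = difference in means = 0.75 − 0.50 = 0.25.
- Slope = Σ(t − 9)y / Σ(t − 9)², with denominator 81 + 9 + 9 + 81 = 180.
- Cohort 1: (−3 + 3 + 9)/180 = 0.0500. Cohort 2: (3 + 9)/180 = 0.0667.
- Slope difference over 18 months = (0.0500 − 0.0667) × 18 = −0.30.
- Fitted cohort difference at month 18 = 0.25 − 0.0167 × 9 = 0.10.

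**Other calendar mappings.** The label main effect runs from zero slope variance to the largest value tried. The last two columns apply only if a label-by-time term is fitted.

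| T0–T3 (months) | x | Label main effect | Slope difference over follow-up | Fitted difference, last visit |
|---|---|---|---|---|
| 0/6/12/18 | – | 0.25 to 0.37 | −0.30 | 0.10 |
| 0/3/6/12 | 0 | 0.25 to 0.22 | +0.11 | 0.31 |
| 0/3/6/12 | 0.5 | 0.375 to 0.39 | −0.06 | 0.34 |
| 0/3/6/12 | 1 | 0.50 to 0.56 | −0.23 | 0.37 |
| 0/3/6/18 | 0 | 0.25 to 0.27 | −0.07 | 0.20 |
| 0/3/6/18 | 0.5 | 0.375 to 0.45 | −0.25 | 0.22 |
| 0/3/6/18 | 1 | 0.50 to 0.63 | −0.43 | 0.23 |
| all six visits | 0 | 0.33 to 0.36 | −0.09 | 0.29 |
| all six visits | 0.5 | 0.33 to 0.46 | −0.34 | 0.14 |
| all six visits | 1 | 0.33 to 0.55 | −0.60 | 0.00 |

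The true value is 1.00 with no loss, and no row recovers it. Each cohort's own slope stays positive throughout, at about 0.65 to 1.29 D over follow-up.

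**Cohort-relative mapping.** Suppose T0 to T3 are 0/3/6/12 months from each cohort's own start. With x = 0.5 both cohorts follow (0, 0.5, 1, 1). The deviations from the mean time of 5.25 give Σ = 78.75, and the slope is (−1.125 + 0.75 + 6.75)/78.75 = 0.081 per month, or about 0.97 D over 12 months. The two paths are identical, so the label coefficient is about 0.

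**With time-varying exposure.** Categorical calendar visit plus an exposure term that follows the assumed path returned 1.00 D under every calendar mapping tried. The 0/6/12/18 case shows what remains estimable. Write E for the effect at completion and P6 and P12 for the effect 6 and 12 months later. The cohort differences are then E at month 6, P6 − E at month 12, and P12 − P6 at month 18. Only month 6 compares treated with untreated; the later visits compare different times since completion.

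**The case against.** The strongest objection is that the timeline is not settled. Table 2 schedules some measures before, during and after the assigned cohort's intervention, and others 6 months after it. This allows T0 to T3 to follow each cohort's own intervention. The Design section, which has both groups measured at each of T0 to T3, points to calendar time. The doubt stands, and it makes any size conditional. It does not rescue the model: under the cohort-relative reading the label has nothing to estimate, and the benefit sits in a common before-after slope with no control.

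A reader might infer that the planned test would show a negative trend. The article does not support that as a fact. It says only that treatment status will be tested as a predictor, and every negative figure needs a label-by-time term that it does not state. Even with that term, one scenario gives +0.11 D. The −0.60 D figure uses all six visits, whereas Aim 3 names four; over the four-visit mappings the lowest value is −0.43 D. For the food security score, where higher is worse, the signs reverse.

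A reader might also infer that the model cannot show a benefit at all, or that the primary analysis is compromised. Neither follows. Each cohort's own slope stays positive, and the Aim 1 contrasts at 3 and 6 months fall before Cohort 2 has received the intervention.

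Finally, the article uses neither the word fixed nor the word linear, and a full analysis plan may code exposure differently. Both readings are inferences, from the Level 2 placement and the single slope. But the article does assign each term to a level. If the full plan differs, this paragraph misdescribes it and still needs correcting.

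**Conclusion.** The point holds in this limited form and should be fixed before the final analysis. As written, the Aim 3 treatment coefficient contrasts early with late start and does not estimate the program's long-term effect. For a fully sustained effect D, the label main effect is about 0.22 to 0.63 D under calendar mappings and about 0 under a cohort-relative one. If a label-by-time term is added, the slope difference lies between about −0.60 and +0.11 D over follow-up for an outcome where higher is better. A lasting benefit could therefore be misread as small or fading.

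That the label does not measure the long-term effect follows from the stated model and crossover schedule. The sizes rest on the assumed effect path, the assumed variances and the unstated months of T1 to T3. The point concerns a non-primary aim.

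**What to change.** In Aim 3:

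- Enter exposure as a time-varying Level 1 term: not yet started, during, end of intervention, time since completion.
- Include calendar visit as a categorical fixed effect, keep the participant random effects and account for center. Whether to keep a random slope is a modelling choice and not part of this change.
- State which months T0 to T3 denote.
- Assess durability as the change from end of intervention to 6 months after it. Include the month-12 comparison of Cohort 1 (about 6 months after completion) with Cohort 2 (just completed).
- State that visits from month 12 have no untreated concurrent comparison, so results there are not a randomized treated-versus-control contrast.

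The cost is revised wording and the recoding of one variable, with no new data. The price is some loss of precision and a more modest claim at 18 months. The article reports 18-month collection as ongoing and preliminary analysis as under way, so the change should be recorded before the final analysis.
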